## Methods/design

This is a multicenter, open-label, prospective cohort study comparing outcomes of MIPG (trial procedure) and MITG (standard of care, control group). We expect to enroll a total of 60 patients in this study (30 per group). Patients will be recruited from and treated at MD Anderson Cancer Center, Mayo Clinic, Memorial Sloan Kettering Cancer Center, Yonsei University, and Keio University, after Institutional Review Board approval for each institution. We plan to enroll at least 20 patients each from Asian (Keio University and Yonsei University) and US (MD Anderson, and Mayo Clinic Minnesota, and Memorial Sloan Kettering Cancer Center) institutions. The total study duration is expected to be 60 months (including enrollment and follow-up). We will prospectively collect PROs longitudinally for a 1-year period. Other clinical factors will also be collected to investigate factors associated with improved PROs.

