#### Details of surgery

After adequate preoperative evaluation, patients who are judged to be physiologically capable of undergoing resection, viewed as having resectable lesions, and without evidence of metastatic disease will undergo MITG or MIPG as per their choice and the surgeon’s discretion. We do not consider randomization feasible because patients often have strong preferences regarding MITG and MIPG. After MITG, a Roux-en-Y reconstruction is performed, whereas after MIPG, an anti-reflux reconstruction technique is chosen by the surgeon (double-tract reconstruction [17] or the double-flap technique [18]) (Fig. 2). All participating surgeons need to have performed at least 30 robotic gastrectomies before enrolling patients into the study, and at least 10 of these procedures need to have used the specific type of reconstruction technique (e.g., double-flap reconstruction after proximal gastrectomy) that the patient will receive. Details of the reconstruction techniques are determined by the surgeon. Patients will undergo standard postgastrectomy care at each institution during their hospital stays. A feeding jejunostomy can be placed for postoperative nutritional support at the surgeon’s discretion. These surgical procedures can be performed with a laparoscopic or robotic approach. Patients who undergo conversion to open laparotomy will be excluded from the study analyses, since conversion is expected to impact postoperative recovery. Patients who are found to have metastatic disease during surgery will also be excluded from the study analyses, regardless of whether the patient completed gastrectomy or not. Those excluded from the study analyses will be considered screening failures to allow for additional enrollees to meet the accrual target.

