### Statistical methods

The primary outcome is appetite level score (with 0 being the best and 10 being the worst) according to the MDASI-GI + (Question #8) at 3 months after surgery. We will enroll a total of 64 patients in order to have 60 evaluable patients at 3 months after surgery (i.e., assuming a 5% attrition rate). With 30 patients expected in each cohort, this study will have 80% power to detect a one-point difference in appetite level score using a two-sample *t*-test with a 5% significance level and assuming a common standard deviation of 1.35 (nQuery Advisor 7.0). We will also compare serum ghrelin levels at 3 months after surgery. For the primary analyses, we will apply the inverse probability treatment weights using propensity scores for assessing the difference between the two surgical groups. Inverse probability weighting is applied by weighting the outcome measures by the inverse of the probability of an individual with a given set of covariates being assigned to their treatment (i.e., propensity score). The propensity scores will be derived through fitting a multiple logistic regression model with MIPG (vs. MITG) as the outcome variable. Then, in the presence of measured confounders, we can estimate the difference between the two treatment groups via inverse probability weighting of the study subjects. For the regression analyses described below for assessing the “surgical procedure” effect, the inverse probability treatment weights using propensity scores will be applied as appropriate in addition to any standard statistical methods. The two-sample t-test or Wilcoxon rank-sum test will also be used to compare the appetite level or ghrelin level at 3 months, as well as the percent change from baseline, between the two cohorts. We will longitudinally collect PROs (using the fully translated MDASI-GI +) and compare specific items and overall scores as well as body weight, body mass index, and albumin and hemoglobin levels at 1, 3, 6, and 12 months after surgery in the cohorts. A linear mixed effects model will be fit to assess the change in QoL over time while accounting for potential intra-patient correlations. “Time” points will be included as a fixed effect, and “patient” will be included as a random effect. The surgical procedure received and use of adjuvant or neoadjuvant therapy will be included as covariates. Similar analyses will be performed to assess the changes in body weight, body mass index, and albumin and hemoglobin levels over time. The number of LNs examined pathologically, incidence of postoperative complications, operating room time, blood loss, and length of hospital stay will be compared. Continuous variables (such as length of hospital stay) will be assessed using the two-sample t-test or Wilcoxon rank-sum test. Categorical variables (such as type and severity of complications) will be assessed using Fisher’s exact test. Local–regional recurrence-free and overall survival will be estimated using the Kaplan–Meier method, and Cox regression analyses will be performed to assess the association with patient characteristics and surgical procedure received. The 3-year loco-regional recurrence rate will be estimated along with the 95% confidence interval. Missing data will be excluded from analysis and no missing data imputation will be performed. Sensitivity analyses to investigate factors associated with PRO scores, including but not limited to country (west vs. east), tumor location, types of reconstruction after PG, use of neoadjuvant and adjuvant therapy, use of jejunostomy or nutrition status, on PRO scores will be performed.

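### Complications and surgical outcomes are compared by unweighted two-sample tests in cohorts formed by choice, while the planned propensity weights cover only the primary and regression analyses

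*Protocol article*

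**What the plan says.** Allocation is not randomised. Under Details of surgery, patients "will undergo MITG or MIPG as per their choice and the surgeon’s discretion", and the reason given is "We do not consider randomization feasible because patients often have strong preferences regarding MITG and MIPG". Postoperative management is local: "Patients will undergo standard postgastrectomy care at each institution during their hospital stays".

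Statistical methods gives the weights two uses. The first is the primary analysis: "For the primary analyses, we will apply the inverse probability treatment weights using propensity scores for assessing the difference between the two surgical groups". The second is the regression models: "For the regression analyses described below for assessing the “surgical procedure” effect, the inverse probability treatment weights using propensity scores will be applied as appropriate", alongside standard methods.

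The same section then lists lymph node count, complications, operating time, blood loss and length of stay for comparison and names the tests. For continuous outcomes: "Continuous variables (such as length of hospital stay) will be assessed using the two-sample t-test or Wilcoxon rank-sum test". For categorical outcomes: "Categorical variables (such as type and severity of complications) will be assessed using Fisher’s exact test". No weight, covariate or stratum is attached to either. The sensitivity analyses that close the section, by country, tumour location, therapy and so on, concern patient-reported outcome scores only.

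**The concern.** A two-sample test asks whether two groups have the same outcome distribution. In a randomised trial that is the same as asking whether the procedure has an effect. In cohorts formed by choice it is not, because the groups may differ before surgery.

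The protocol gives reasons to expect such differences. The Background says proximal gastrectomy is commonly used for cT1 tumours in South Korea and Japan, while total gastrectomy is the Western standard. Eligibility sets no limit on stage among non-metastatic tumours. Length of stay will reflect each hospital's own care. The Discussion faults an earlier survey of total versus proximal gastrectomy because stage and extent of node dissection were unbalanced, and node count and complications are open to the same imbalance here.

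The Abstract and Rationale make safety of the trial procedure a central hypothesis, Study objectives places it under the secondary objective, and the Discussion says the study will determine it. A crude contrast could show an advantage that is only case mix, or cancel a real harm.

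**Working it through.** **The plan's own figure.** The only design calculation is for appetite: 30 per group, difference 1, SD 1.35, 5% level (taken as two-sided). The noncentrality is 1 / (1.35 × √(2/30)) = 2.87 on 58 degrees of freedom, which gives 80.5% power. The stated 80% is reproduced. No design figure is given for the safety or surgical comparisons.

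**Inputs for the check.** From the protocol: 30 per procedure and a 5% level. Assumed, because the protocol gives no values: an equal split of 30 per region (it promises only at least 20 from each), uptake of MIPG of *q* in one region and 1 − *q* in the other, and the outcome difference between regions or risk strata. The procedure effect is set to zero throughout.

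**Continuous outcomes.** Let the outcome differ by *k* within-region SDs between regions.
- Crude bias = *k*(2*q* − 1).
- SD within a cohort = √(1 + *k*²*q*(1 − *q*)).
- Noncentrality = (bias / SD) × √15, referred to a noncentral t with 58 degrees of freedom.

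Example, *k* = 1 and *q* = 0.7: bias 0.40; SD √1.21 = 1.10; noncentrality 0.364 × 3.873 = 1.41; rejection 28.3%.

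| Uptake | *k* = 0.5: bias | t-test rejects | *k* = 1: bias | t-test rejects |
|---|---|---|---|---|
| 60/40 | 0.10 SD | 6.6% | 0.20 SD | 10.5% |
| 70/30 | 0.20 SD | 11.5% | 0.40 SD | 28.3% |
| 80/20 | 0.30 SD | 20.2% | 0.60 SD | 56.4% |

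Simulated ranges for the same settings are about 7–19% and 12–57%, within one to two points of the formula. At *k* = 1, simulated Wilcoxon rejection is 10.5%, 26.9% and 55.5%, close to the t-test. Regional splits of 20/40 or 40/20 lower the t-test figures to 24–25% at 70/30 and about 50% at 80/20.

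**Complications.** Suppose risk depends only on a binary stratum, and a share *q* of the MIPG cohort and 1 − *q* of the MITG cohort is in the low-risk stratum.
- MIPG risk = *q* × low + (1 − *q*) × high.
- MITG risk = (1 − *q*) × low + *q* × high.
- Rejection by Fisher's test follows by enumerating all tables with 30 per arm.

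Example, risks 15% and 45%, *q* = 0.7: MIPG 0.7 × 15 + 0.3 × 45 = 24%; MITG 0.3 × 15 + 0.7 × 45 = 36%; crude difference −12 points.

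| Shares | 15% vs 30%: crude bias | Fisher rejects | 15% vs 45%: crude bias | Fisher rejects |
|---|---|---|---|---|
| 60/40 | −3 points | 2.9% | −6 points | 4.6% |
| 70/30 | −6 points | 4.6% | −12 points | 11.2% |
| 80/20 | −9 points | 7.7% | −18 points | 24.1% |

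With balanced cohorts Fisher's test rejects about 2.4–2.6%, so it starts well below 5%. The bias also works as a mask: a true excess of 12 points after MIPG plus a case-mix bias of −12 points gives a crude difference of zero.

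**What weighting does.** In simulation with a single binary confounder shifting the outcome by 1 SD, weighting by the propensity score with a robust standard error gives bias of about zero and rejection of 2.8%, 3.3% and 4.5% at 60/40, 70/30 and 80/20. This is a favourable case: one measured, correctly modelled confounder.

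**The case against.** Four points can be made for the plan.

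- *The weighting sentence is loose.* It applies weights where appropriate and alongside standard methods, and a two-group mean comparison is formally a one-covariate regression. But the subject of the sentence is the regression analyses, and the named tests are not presented as such. The most this shows is ambiguity, which is better settled before the data are seen.
- *The article is condensed.* An analysis plan that is not shown may weight these endpoints, so the absence of adjustment is certain only for the article. That stands. But the article does not leave the choice open: it names the tests.
- *The inflation is assumed, and small in milder settings.* This stands. For complications, moderate confounding leaves Fisher's test at or below 5% in several settings. With risks of 20% and 30% it rejects in 2.7%, 3.4% and 4.7%. The bias in the estimate remains (2, 4 and 6 points), but false rejection is then not the main problem.
- *Weighting has its own cost.* With five centres, several prognostic factors and about 60 patients, weights could be extreme, above all for sparse complications, and a wide interval can also miss harm. This stands and limits how large the propensity model should be.

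A reader might also infer that the study sets out to show MIPG to be as safe as MITG. The document does not say so. It hypothesises that the procedure is safe and says safety of both procedures will be investigated, with no equivalence or non-inferiority aim, margin or power.

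**Conclusion.** The point holds for the secondary safety and surgical endpoints. As written, complications, length of stay, operating time, blood loss and node count are compared without adjustment in cohorts formed by choice, although the plan accepts elsewhere that weighting is needed. The direction and size of the resulting bias are unknown. What follows from the document is that these contrasts cannot separate procedure from case mix and institution.

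The size is conditional on assumed imbalances. It ranges from negligible (Fisher's test still near 3% with a 3-point bias) to serious (the t-test above 50% with a 0.6 SD bias). None of these percentages predicts this study's error rate, and a reader should not take the upper values as expected. The primary appetite comparison is weighted and is not touched. The crude tests remain valid as descriptions of the two cohorts. The change is worth making because safety is a central hypothesis, but it does not threaten the main result.

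**What to change.** In Statistical methods, state that for complications, length of stay, operating time, blood loss and lymph node count the between-procedure estimate is a weighted risk difference (binary) or weighted mean difference (continuous). Use the primary analysis weights, with region (Asia versus US) in a small propensity model, and robust or bootstrap 95% confidence intervals. Report the distribution of the weights. Keep the t-test, Wilcoxon and Fisher results as labelled crude descriptions, and say that no conclusion about procedure safety is drawn from them.

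The cost is a few sentences and some programming. No new data are needed: treating institution, tumour location and preoperative therapy are already on the collection list, where the medical record has them. The drawbacks are wider intervals than the crude ones, possibly unstable weights for rare complications in about 60 patients, and no protection against unmeasured confounders.

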#### Safety measures

The rate and types of postoperative complications within 90 days after surgery, length of post-operative hospital stay, and rate of post-discharge re-admission within 90 days after surgery will be recorded.

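### Severity of complications is ordered, but the plan compares it with Fisher's exact test, which ignores the order: a valid but inefficient choice for this secondary comparison

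*Protocol article*

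**What the plan says.** In the protocol article, Statistical methods, the test for complications is fixed in one sentence: "Categorical variables (such as type and severity of complications) will be assessed using Fisher’s exact test". The sentence before it gives the rule for other variables: "Continuous variables (such as length of hospital stay) will be assessed using the two-sample t-test or Wilcoxon rank-sum test". So a rank test is already in the plan, but for continuous variables only.

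Under Safety measures the article lists "The rate and types of postoperative complications within 90 days after surgery", together with length of stay and re-admission. Severity is not in that list. It appears only as an example in the sentence on Fisher's exact test. The article gives no grading scale, number of grades, expected grade rates or power for complications.

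The only power statement concerns the primary endpoint: "With 30 patients expected in each cohort, this study will have 80% power to detect a one-point difference in appetite level score".

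**The concern.** Type and severity are treated as the same kind of variable, and they are not. Types of complication are labels without an order. Grades of severity run from better to worse. On a table of two groups by k grades, Fisher's exact test sees only labels, so it responds to any difference between the groups and cannot favour the pattern in which one operation is consistently worse.

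Safety of the proximal operation is one of the article's central hypotheses. With about 30 patients per group any comparison of complications has limited power. A test that discards the order makes a non-significant severity result more likely when a consistent difference exists, and such a result is easily read as reassurance. The choice of test is written into the article, so this is not a detail left to a fuller document.

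**Working it through.** **1. The plan's own figure.** Inputs from Statistical methods: 30 per group, a difference of 1 point, "with a 5% significance level and assuming a common standard deviation of 1.35". The sidedness is not stated; two-sided is assumed.

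- Normal approximation: 1 / (1.35 × √(2/30)) = 1 / 0.3486 = 2.869. Then 2.869 − 1.960 = 0.909, and Φ(0.909) = 81.8%.
- Noncentral t: 80.5%.
- Attrition: 60 / 0.95 = 63.2, rounded up to the 64 in the article.

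The stated 80% reproduces. It concerns appetite and says nothing about complications.

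**2. Why Fisher's test ignores order.** With column totals c_j, first-group counts a_j, total N and first-group size n₁, the probability of a table is ∏ C(c_j, a_j) / C(N, n₁). The p-value sums the probabilities of all tables no more likely than the one observed. The product does not depend on the order of the columns, so neither does the p-value. The rank-sum statistic is W = Σ m_j a_j, where m_j is the mid-rank of grade j. It changes when grades are re-ordered.

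**3. Size under assumptions.** Assumed: 30 against 30, two-sided 5%, reference distributions with 50% to 70% free of complications, and a common odds ratio (OR) shifting every cumulative odds. Example with reference 60/20/15/5% and OR 3:

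- Cumulative probabilities 0.60, 0.80, 0.95 have odds 1.5, 4, 19.
- Divided by 3: 0.5, 1.333, 6.333.
- Back to probabilities: 0.333, 0.571, 0.864.
- Shifted distribution: 33.3/23.8/29.2/13.6%.

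Simulated power, 3,000 trials per scenario, exact Fisher test against tie-corrected rank-sum test:

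| Reference distribution (%) | OR 2 | OR 3 | OR 4 |
|---|---|---|---|
| 5 levels, 60/12/15/10/3 | 17.2 vs 27.9 | 41.5 vs 61.5 | 62.8 vs 82.6 |
| 5 levels, 50/15/15/15/5 | 18.5 vs 31.4 | 42.7 vs 62.7 | 61.7 vs 83.0 |
| 5 levels, 70/10/10/7/3 | 15.5 vs 26.5 | 37.1 vs 57.3 | 58.2 vs 78.4 |
| 4 levels, 60/20/15/5 | 18.5 vs 26.8 | 44.9 vs 60.9 | 65.2 vs 81.8 |
| 3 levels, 60/25/15 | 21.6 vs 28.5 | 49.8 vs 61.2 | 71.1 vs 80.7 |
| 3 levels, 70/15/15 | 18.3 vs 26.3 | 45.2 vs 56.8 | 69.8 vs 78.5 |

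The gain is about 7 to 12 points with 3 levels, 8 to 17 with 4 and 11 to 21 with 5. At OR 1 the rejection rates were 4.3% to 5.6% (Fisher) and 4.8% to 5.6% (rank-sum), so the gain is not bought with false positives. Separate simulations with the exact rank-sum test gave about 6 to 16 points for 3 or 4 levels and about 9 to 21 for 4 or 5 levels. The overall range is about 6 to 21 points.

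**4. Smaller effects.** The Discussion quotes late complications of 14.3% after total and 10.8% after proximal gastrectomy in another trial: (0.143/0.857) / (0.108/0.892) = 0.1669 / 0.1211 = 1.38. At that odds ratio, with three assumed 4-level distributions, Fisher has 7.0% to 8.0% power and the rank-sum test 8.1% to 10.0%, a gain of about 1 to 2 points. At OR 1.5 the gain is about 3 to 4 points.

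**5. Where the rank test loses.**

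- None/minor/major 60/15/25% against 55/40/5%: Fisher 69.1%, rank-sum 6.3%.
- 60/30/10% against 60/10/30% (same share without complications, severity moved from minor to major): Fisher 58.1%, rank-sum 9.1%.

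**The case against.** The strongest reply is that nothing here is invalid. Fisher's exact test controls the type I error, the comparison is secondary, no power is claimed for it, and the primary analysis and sample size are untouched. All of that stands.

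A reader might infer that the plan gives up some fixed amount of power, say 9 to 21 points, in its safety comparison. The documents do not support this, for two reasons. The grades, their rates and the odds ratios are all assumed. And the safety comparison is wider than severity: rate, type and re-admission are binary or nominal, so they have no order to lose, and length of stay already has a rank-test option.

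It is also fair that the gain nearly vanishes for modest effects. The odds ratio of 1.38 is only a rough anchor, since it concerns late events in a different trial, but it is the only such contrast in the article. At that size neither test is useful with 30 per group.

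An unordered test is defensible when the pattern of difference is unknown. In the two scenarios of step 5 the rank test gives up 63 and 49 points, more than its largest gain, so this downside must be stated plainly. Against it, the natural safety question is directional, namely whether one operation is worse, and a table by grade would expose a pattern that the rank test misses.

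Finally, the full protocol may define severity as major complication yes or no. Fisher's test would then be standard and the point would not apply. Nor does the change cure confounding: the groups are not randomised, the rank-sum test is as unadjusted as Fisher's, and a non-significant result from either would not show that the proximal operation is safe.

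**Conclusion.** The point holds as a minor matter of efficiency. The article names severity and assigns it a test that ignores its order, although a test that uses order stands in the preceding sentence. The gain from changing is about 6 to 21 points of power at odds ratios of 2 to 4 and about 1 to 2 points near 1.4. This assumes 30 per group (expected but not fixed by the design, since the procedure is chosen), a two-sided 5% level, 3 to 5 ordered grades and a proportional-odds shift. None of the grade distributions or effects comes from the documents. The conclusion is confined to the severity comparison. It does not make the planned test invalid or any stated figure wrong.

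**What to change.** In Statistical methods, keep Fisher's exact test for type of complication and for binary variables such as any complication and re-admission. Add that severity, taken as each patient's worst grade within 90 days with no complication as the lowest level, will be compared with an exact Wilcoxon rank-sum test. Report with it an ordinal effect estimate (a common odds ratio, or the probability of a worse grade) with its 95% confidence interval, and the full grade-by-grade table by group. If severity is to be analysed only as a binary variable, state the cut in advance and leave Fisher's test in place.

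The cost is about one sentence. It needs no new patients, data or procedures. The price in power is the possible loss when the operations trade minor for major complications, which is why the grade table belongs in the same sentence. The choice should be fixed before outcomes are seen.
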